**Recruitment**

All English and Spanish-speaking pregnant patients initiating prenatal care at SFGH Women’s Health Center are eligible to participate. We will offer study enrollment to English and Spanish speaking pregnant patients initiating prenatal care at SFGH WHC. We will include women who are 16 years or older and are capable of providing informed consent. We will exclude women who do not speak either English or Spanish, women who are not able to give informed consent, women younger than 16 years old and women who obtained an HIV test during the index pregnancy prior to initiation of prenatal care at SFGH. In addition, we will exclude pregnant women who are known to be infected with HIV at initiation of prenatal care at SFGH.

We will be posting flyers in the Women’s Health Clinic so that patients will be aware of the study. We will also be providing only a small monetary incentive for their participation. We will reimburse the subjects $10 for their participation in the study if such funding is available at the time of subject recruitment. Specifically, we will reimburse $5 at the completion of the pre-test questionnaire and $5 at the completion of the post-test questionnaire. Additionally, bilingual/bicultural research staff will be conducting recruitment, administering the study consents and surveys. We will also be using a validated low-literacy scale to measure satisfaction.

**Informed Consent**

We will obtain written informed consent from each study participant. The consent will review the purpose of the research, what each participant will undergo, the time that will be required, the follow-up provided for positive tests, the risks and benefits, the protocols for maintaining confidentiality, and the voluntary nature of participation. This will take place at the nursing intake visit as mentioned above, by the research staff member recruiting the subject’s participation. The location is at the Women’s Health Center (5M) at SFGH. Subjects will be given time to consider study participation and research staff will be readily available to answer questions from potential subjects. In addition, all eligible patients will receive the standard prenatal HIV testing brochure. All women electing to undergo HIV testing will also sign the HIV testing consent form consistent with California state law.

**Statistical Analysis**

We will measure the receipt of results as a proportion of those undergoing testing who receive their results before the onset of labor. We will compare the proportions between the 2 groups using the χ² test. We will calculate a satisfaction score for all study participants using the Decisional Conflict Scale which has been validated in many study populations. (20) We will compare mean satisfaction scores between the 2 groups using the Student t-test (if the distribution is parametric) or Wilcox rank-sum test (if the distribution is non-parametric). Lastly, we will conduct multivariate logistic regression to assess independent predictors using STATA SE8. We will test for interaction and stratify the multivariate analysis accordingly. We will conduct a strict intention-to-treat analysis. We will develop the data collection forms with the date and alphanumeric code on each page. Each variable will be named and coded. We will utilize a Microsoft ACCESS relational database. We will pretest the data management system with “dummy” data. We will promptly enter the data after collection and set criteria within the ACCESS database to minimize the likelihood of incorrect data entry. Once all data is entered, we will edit the database, checking for missing data, illogical data and outliers. We will log any changes made in the database during the editing process and freeze the final database before importing the data into statistical analysis software. We will then analyze and archive the database.

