**Specific Aims**

1. To compare the acceptability of standard and abbreviated HIV counseling/testing strategies among a sample of low- income, urban, ethnically diverse prenatal patients.
2. To create an abbreviated HIV counseling/testing protocol compatible with the new California prenatal HIV testing law (AB 1676) that can be used in prenatal settings throughout the state.
3. To compare the proportion of enrolled pregnant women tested for HIV by the standard, risk-based vs. abbreviated counseling/testing strategy.
4. To compare the proportion of HIV-tested pregnant women receiving their HIV test results by the standard vs. abbreviated counseling/testing strategy.

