**Preliminary Studies**

A retrospective chart review of pregnant women accessing prenatal care at SFGH Women’s Health Clinic (WHC) showed that due to the change in standard of care at SFGH, from a dedicated HIV counseling and testing service to provider-performed counseling and testing, prenatal HIV testing uptake at SFGH has increased from 52% in 2003 to 93% as of April 2006. In a cross-sectional study of prenatal patients at SFGH WHC, nearly 70% of women surveyed supported routine testing as compared to 27% who supported elective testing. This support for routine prenatal HIV testing was comparable to these women’s attitudes towards routine rubella screening (63% support) and routine gonorrhea/chlamydia screening (77% support). The study we propose would be the natural next step in more specifically evaluating the routinization and streamlining of HIV testing in the prenatal care setting through the use of a rigorous randomized methodology.

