**Study Design**

This will be a randomized controlled, non-inferiority trial comparing two HIV testing strategies among English and Spanish-speaking patients presenting for prenatal care at SFGH WHC over the course of approximately one year. Eligible participants will be randomized by study personnel to either standard HIV counseling and testing (control arm) or abbreviated counseling and testing (study arm). See Appendix 1. Participants will receive a standard prenatal HIV testing brochure, undergo one of two HIV counseling/testing strategies, submit blood for an HIV-1 antibody test, and will follow-up with their medical provider for HIV test results. Upon completion of counseling, participants will undergo a short, structured (Pre-test) questionnaire administered by study staff. Following testing and receipt of results, participants will complete a second (Post-test) structured questionnaire administered by study staff. Eligible women presenting to SFGH physician or midwife prenatal clinics will be recruited, consented and randomized by study staff to either the standard or abbreviated testing strategy. The outcomes studied will be patient satisfaction and the proportion of study participants who undergo HIV testing. Potential confounder variables to be measured will include demographic characteristics, prior HIV testing history, knowledge about HIV/AIDS, attitudes towards HIV testing, HIV test result, and type of provider (physician versus midwife).

All procedures will take place in SFGH Women’s Health Clinic. Time required of the subjects outside of routine prenatal care visits includes approximately 10 minutes for recruitment and randomization, 5-10 minutes for the pre-test questionnaire, and 5 minutes for the post-test questionnaire. If the patient is lost to follow-up and can no longer be reached upon visiting the clinic, the follow-up interview will be attempted to be conducted via telephone. We will specifically ask the participant permission on whether or not we can leave a simple message on her voicemail if she is lost to follow-up.

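### Receipt of results is compared between arms only among women who were tested, a group formed after randomisation, so the comparison is not protected by randomisation and does not fit the promised strict intention-to-treat analysis

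*Protocol*

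**What the plan says.** Aim 4 in the protocol's Specific Aims is "To compare the proportion of HIV-tested pregnant women receiving their HIV test results by the standard vs. abbreviated counseling/testing strategy". The Statistical Analysis section carries this out with the same denominator: "We will measure the receipt of results as a proportion of those undergoing testing who receive their results before the onset of labor". The next sentence gives the method: "We will compare the proportions between the 2 groups using the χ² test". Later in the same section, with no exception for any endpoint, comes "We will conduct a strict intention-to-treat analysis".

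Three other places bear on who is in that denominator:

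- Study Design gives the order of events after randomisation. Participants "undergo one of two HIV counseling/testing strategies, submit blood for an HIV-1 antibody test, and will follow-up with their medical provider for HIV test results".
- Informed Consent shows that the blood test is a choice, not a condition of participation: "All women electing to undergo HIV testing will also sign the HIV testing consent form consistent with California state law".
- Aim 3 makes uptake of testing an outcome in its own right, with all enrolled women as denominator: "To compare the proportion of enrolled pregnant women tested for HIV by the standard, risk-based vs. abbreviated counseling/testing strategy".

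No version of result receipt with all randomised women as denominator is given. Sample Size names the decisional conflict score as the primary outcome, so result receipt is a secondary matter.

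**The concern.** Randomisation makes the two arms comparable at the moment of allocation. Being tested comes later, after the counselling that differs by arm. If one strategy leads some women to test who would have declined under the other, the two tested groups contain different kinds of women. A difference in result receipt between them then mixes two things: an effect of the strategy on the results step, and a difference in who was tested. An unadjusted χ² test cannot separate them.

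What is at stake is the reading of Aim 4. The protocol's Background ties prevention of perinatal transmission to diagnosis before delivery. The figure that serves this purpose is the share of all randomised women who were tested and knew their result before labor. A strategy that brings in more hesitant women could raise that share while its tested-only proportion falls.

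**Working it through.** **The plan's own figure.** The only sample size in the protocol is for the decisional conflict score: margin 5.625, SD 18.75, one-sided alpha 0.05, power 80%. The normal approximation is n = 2 × (1.645 + 0.842)² × (18.75 / 5.625)² = 137.4, rounded up to 138 per arm. With the noncentral t distribution, power is 0.7998 at 138 and 0.8023 at 139, so the stated 139 per arm reproduces. Nothing below changes it. The protocol gives no power or expected rate for result receipt.

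**Women leaving the denominator.** Preliminary Studies reports that "prenatal HIV testing uptake at SFGH has increased from 52% in 2003 to 93% as of April 2006". At 93% uptake, 139 × 0.93 = 129.3 women per arm are tested and 139 × 0.07 = 9.7 are not, so about 10 per arm drop out of the Aim 4 comparison.

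**How far the two denominators can diverge.** Only the 93% and the 139 come from the protocol. Assumed: uptake of 98% in the abbreviated arm; 95% receipt in women who would test under either strategy; receipt r in the extra 5% who test only under the abbreviated strategy.

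- Standard arm: tested-only 95.0%; all randomised 0.93 × 0.95 = 88.35%.
- Abbreviated arm: all randomised 0.93 × 0.95 + 0.05 × r; tested-only is that figure divided by 0.98.

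| r (assumed) | Tested-only, abbreviated | Difference from standard | All randomised, abbreviated | Difference from standard |
|---|---|---|---|---|
| 95% | 95.0% | 0 | 93.1% | +4.75 points |
| 50% | 0.9085 / 0.98 = 92.7% | −2.3 points | 90.85% | +2.5 points |
| 0% | 0.8835 / 0.98 = 90.2% | −4.8 points | 88.35% | 0 |

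In each row the strategy leaves receipt unchanged for women who would test either way. Any tested-only difference therefore comes entirely from who was tested.

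**Equal uptake.** With 93% in both arms and the same kind of women tested, both differences are 0. Equal uptake alone does not guarantee this. In the extreme case where the untested 7% are entirely different women in each arm, 86% test either way and 7% test under one strategy only. Suppose receipt is 95% in all of them except the abbreviated-only 7%, where it is 50%. The tested-only figures are then 95.0% and (0.86 × 0.95 + 0.07 × 0.50) / 0.93 = 91.6%, a gap of 3.4 points.

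**Against sampling error.** In the 50% row, about 129 and 136 women are tested.

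- Tested-only: SE = √(0.95 × 0.05 / 129.3 + 0.927 × 0.073 / 136.2) = 2.9 points, for a difference of −2.3.
- All randomised: SE = √(0.8835 × 0.1165 / 139 + 0.9085 × 0.0915 / 139) = 3.7 points, for a difference of +2.5.

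Both differences are smaller than one standard error.

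**The case against.** The conditional question is deliberate. Aim 4 asks about tested women and the analysis does what the aim says. The arms differ in post-test as well as pretest procedures, so receipt among tested women is a sensible measure of the results step. This stands: the measure need not be deleted or barred from comparison. It does need a label saying what it is conditional on.

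Aim 3 already compares uptake among all enrolled women, and multiplying the Aim 3 and Aim 4 proportions within each arm gives the all-randomised figure. This stands in part. A careful reader could form the product, but the plan provides no test or interval for it.

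A reader might infer that the analysis flatly contradicts the intention-to-treat promise. The protocol does not define the term. If it means only analysis by assigned arm, nothing here moves a woman between arms. The inconsistency arises under the reading that every randomised woman is analysed, which the word strict, used without exception, invites.

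A reader might also infer that the protocol expects uptake to differ by arm. It does not say so. Its hypothesis is equal acceptability, both arms use the same types of staff, and women who test sign the state consent form in either arm. The 25% to 98% range in Background contrasts opt-in with opt-out regions, and the rise from 52% to 93% followed a move away from a dedicated counselling service; neither is the contrast randomised here. Aim 3 shows only that uptake is allowed to differ and will be compared.

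**Conclusion.** The point holds, at a moderate level. Result receipt is compared in a group formed after randomisation and open to influence by the strategy, so the χ² comparison is not a randomised one and does not meet strict intention-to-treat in its full-population sense.

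The bias may be zero. It is zero if uptake and the kind of women tested match across arms. With about 10 of 139 women per arm outside the denominator, and under the assumed 93% against 98% uptake, it runs from 0 to about 5 points; a wider gap in uptake could make it larger. Those figures rest on assumed rates, apart from the 93%.

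The opposite signs in the 50% row might be read as showing that the trial's conclusion would reverse. They show only that the two denominators can point in different directions under chosen rates, by amounts the trial could not tell from zero. The primary outcome, its margin and the 278 participants are untouched.

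**What to change.** In Aim 4 and the Statistical Analysis section, make the intention-to-treat comparison the proportion of all randomised women who were tested and received their result before labor began, counting untested women as not having received it. Report the risk difference with a 95% CI.

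Keep the tested-only proportion as a secondary process measure, stated to be conditional on testing and not protected by randomisation.

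The cost is one added analysis and a wording change in those two places. Testing status is already needed for Aim 3, and receipt before labor for Aim 4, so no new data and no larger sample are required.

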**Trial Protocol**

**Synopsis**

We propose a randomized controlled, non-inferiority trial to evaluate the effectiveness of two HIV testing strategies among 278 pregnant women seeking prenatal care at San Francisco General Hospital. The two strategies will include pretest/post-test counseling using prenatal care nurses and medical providers (control arm; current standard of care at San Francisco General Hospital [SFGH]) and an abbreviated pretest/post-test CDC recommended strategy using prenatal care nurses and medical providers (study arm). We hypothesize that the abbreviated CDC recommended strategy will be equally acceptable to patients as the standard strategy currently used. Eligible participants will include Spanish or English-speaking women seeking prenatal care at San Francisco General Hospital over the course of approximately one year. Eligible women presenting to SFGH physician or midwife prenatal clinics will be recruited, consented and randomized by study staff to either the standard or abbreviated testing strategy. The outcomes studied will be patient satisfaction and the proportion of study participants who undergo HIV testing. Satisfaction will be measured using the validated Decisional Conflict scale.

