**Sample Size**

Our sample size calculation was based on the primary outcome, decisional conflict score. Because this was a non-inferiority trial, the trial was designed to be able to exclude an actual difference between the abbreviated and standard counseling arms of greater than 5.625 (the non-inferiority margin) with respect to the mean decisional conflict score (DCS) in each group. To calculate our sample size, we used a type-I error rate (alpha) of 0.05 with an 80% power, a common standard deviation of 18.75 for the DCS, and a one-sided two group t-test of equivalence in means (equal n's) to arrive at 139 patients in each arm for a total of 278 participants. 20, 21 Assuming 75% participation as was seen in a 1997 study of the same patient population (i.e. those accepting enrollment and randomization), we will need to approach 371 women overall.

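### The analysis section compares the primary score by a plain t-test or rank-sum test and does not carry over the 5.625 non-inferiority margin on which the trial was sized

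*Protocol*

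**What the plan says.** The Study Design section states the design: "This will be a randomized controlled, non-inferiority trial comparing two HIV testing strategies". The Synopsis gives the hypothesis: "We hypothesize that the abbreviated CDC recommended strategy will be equally acceptable to patients as the standard strategy currently used".

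The Sample Size section names the endpoint: "Our sample size calculation was based on the primary outcome, decisional conflict score". The study is described there as "designed to be able to exclude an actual difference between the abbreviated and standard counseling arms of greater than 5.625 (the non-inferiority margin"). The calculation there is a one-sided equivalence-type t-test with equal arms, and its inputs are "we used a type-I error rate (alpha) of 0.05 with an 80% power" and "a common standard deviation of 18.75 for the DCS". It arrives at 139 per arm, 278 in total.

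The Statistical Analysis section is the only text on how outcomes will be analysed. It derives a satisfaction score from the Decisional Conflict Scale, so the score is the primary outcome. It then says "We will compare mean satisfaction scores between the 2 groups using the Student t-test (if the distribution is parametric"), or a rank-sum test if not. The margin is not mentioned there, and it appears nowhere in the protocol outside the Sample Size section.

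**The concern.** A t-test or rank-sum test named without a null value is normally run against no difference. Failing to reject no difference does not show that a difference of 5.625 has been excluded, and excluding that difference is what the trial was sized to do. The rank-sum fallback is further from the design, because it does not test a 5.625-point margin on means at all.

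The direction is also open. The margin is set on a conflict score, where a higher value is presumably worse. The analysis text calls the same score satisfaction, which would suggest that higher is better. A one-sided margin has no meaning until the direction is written down.

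At stake is the error rate of the main claim. If a non-significant p-value were taken as support for equal acceptability, the chance of wrongly endorsing the abbreviated strategy would no longer be the stated 5%. It would also rise as fewer women were analysed.

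**Working it through.** **Inputs.** From Sample Size: margin 5.625, SD 18.75, alpha 0.05 one-sided, power 80%, 139 per arm. Two assumptions are not in the protocol: a true difference of 0 for the sizing, and higher DCS is worse. The sidedness of the test in Statistical Analysis is not given, so both cases are shown.

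**1. Reproduce the plan's sample size.**
- Normal approximation: n per arm = 2 × (18.75/5.625)² × (1.645 + 0.842)² ≈ 137.4, rounded up to 138.
- Exact noncentral t: 139 per arm, power 80.2%.

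The stated 139 is reproduced, which supports the assumed true difference of 0. The sizing is a genuine margin-based calculation.

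**2. Standard error at 139 per arm.** SE = 18.75 × √(2/139) = 2.249, with 2 × 139 − 2 = 276 degrees of freedom. The margin is 5.625/2.249 = 2.50 standard errors.

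**3. What each rule requires of the observed difference (abbreviated minus standard).**
- Margin rule, upper one-sided 95% limit below 5.625: observed difference below 5.625 − 1.65 × 2.249 = 1.91.
- One-sided 0.05 difference test, non-significant: below 1.65 × 2.249 = 3.71.
- Two-sided 0.05 difference test, non-significant: within ±1.969 × 2.249 = ±4.43.

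Observed differences from about 1.9 to 3.7 (one-sided) or 4.4 (two-sided) are therefore non-significant yet do not exclude the margin.

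**4. If the abbreviated arm is truly worse by 5.625** (noncentral t, 276 df):

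| Rule | Probability of the favourable-looking result |
|---|---|
| Margin rule | 5% (simulation 4.99%) |
| One-sided 0.05 difference test non-significant | 19.8% |
| Two-sided 0.05 difference test non-significant | 29.7% (simulation 29.8%) |

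**5. If the arms are truly equal.** The result falls in the gap of step 3 with probability of about 95% − 80.2% = 14.8% (one-sided) or 97.5% − 80.2% = 17.3% (two-sided).

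**6. Effect of fewer women analysed,** two-sided test, true difference 5.625: non-significant 36% of the time at 120 per arm, 44% at 100 and 58% at 70. Under a difference test, loss of data makes a favourable-looking result more likely.

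**The case against.** The strongest reply is that the two sections should be read together. Statistical Analysis gives no null value and no sidedness, and a t-test can be run against a shifted null. Sample Size supplies the margin, the alpha, the one-sidedness and the family of test for this same score. On that reading only a linking sentence is missing, and a statistical analysis plan, which may exist but is not at hand, could supply it.

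Part of this stands. The margin is in the protocol, and the defect is a mismatch between two of its sections. The reply does not dispose of the point, because the protocol is not silent on the test. It names one which, as ordinarily run, does not match the design, and its rank-sum alternative cannot be shifted to a margin on means.

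Several stronger readings are tempting and are not supported:
- *The trial cannot show non-inferiority.* The planned data and the two means are all that is needed to apply the 5.625 bound. Only the stated analysis falls short.
- *A non-significant result will be read as non-inferiority.* The protocol nowhere says so. The Synopsis states equal acceptability as a hypothesis and not as a decision rule. The documents support only that such a misreading could occur.
- *The margin and the analysis concern different endpoints.* Statistical Analysis itself calculates the satisfaction score from the Decisional Conflict Scale, so they are one score.
- *The error rate is 30%.* That is the two-sided end of the range. The only sidedness the protocol states is one-sided, which gives about 20%.
- *Power falls to 70%.* That figure belongs to a two-sided 95% interval, which the protocol does not propose.

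**Conclusion.** The point holds as an inconsistency between Sample Size and Statistical Analysis. Followed as written, the analysis does not test the trial's own hypothesis, and this should be corrected because it governs the primary conclusion.

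The size of the problem depends on how the result would be read. If non-significance were taken as success, the chance of a wrong favourable conclusion at a true difference equal to the margin would be about 20% to 30%, against the stated 5%. This rests on the protocol's SD of 18.75, on 139 analysed per arm and on higher DCS being worse, which the protocol does not state. The sample size itself is sound for the stated margin rule.

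**What to change.** In Statistical Analysis, replace the sentence on comparing mean scores with wording along these lines:

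*The primary analysis estimates the difference in mean DCS, abbreviated minus standard, where a higher score means more conflict [scoring direction to be confirmed]. Non-inferiority is concluded only if the upper limit of the one-sided 95% confidence interval for this difference is below 5.625.*

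For non-normal scores, keep the comparison on the mean difference, for example with a bootstrap confidence limit judged against the same 5.625, and use the rank-sum test only as supportive. Use one name for the score throughout.

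The cost is wording only. Alpha, margin, the total of 278 and the 80% power all stay as they are (80.2% at 139 per arm), and no further data are needed.

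### The primary comparison may switch, on an unstated criterion, to a rank-sum test that does not target the mean difference on which the 5.625 margin and the sample size are defined

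*Protocol*

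**What the plan says.** The protocol's Sample Size section makes the DCS the primary outcome: "Our sample size calculation was based on the primary outcome, decisional conflict score". The trial is to exclude a difference "greater than 5.625 (the non-inferiority margin", and the scale of that difference is explicit: "with respect to the mean decisional conflict score (DCS) in each group". The other inputs are "type-I error rate (alpha) of 0.05 with an 80% power" and "a common standard deviation of 18.75 for the DCS". The calculation is a one-sided two-group t-test in means with equal arms, giving 139 per arm.

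The Statistical Analysis section deals with the same score under the name of satisfaction: "We will calculate a satisfaction score for all study participants using the Decisional Conflict Scale". The rule for testing it has two branches. The first is "We will compare mean satisfaction scores between the 2 groups using the Student t-test (if the distribution is parametric". The second is "Wilcox rank-sum test (if the distribution is non-parametric".

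The section does not say how the distribution will be judged, or whether that is done on pooled or blinded data. It does not connect either test to the margin.

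**The concern.** The two sections do not describe the same primary analysis. One defines success on a difference in means. The other lets the observed scores decide whether a difference in means is tested at all. A rank-sum test asks whether scores in one arm tend to exceed those in the other, and it does not estimate the mean difference. Subtracting 5.625 from the study-arm scores and then ranking gives a test in score points, but that test matches the stated hypothesis only if abbreviated counseling moves the whole distribution by one constant.

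A non-constant effect matters here. If shorter counseling leaves most women unaffected and a minority much more conflicted, the mean registers the full size of the harm, while ranks discount how far the affected women moved. The trial could then declare non-inferiority although the mean difference has reached the limit it was designed to exclude. Whether it did so would depend on a choice made after the scores were seen.

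**Working it through.** **Inputs from the protocol (Sample Size):** margin 5.625, SD 18.75, one-sided alpha 0.05, power 80%, true difference 0, equal arms.

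**Step 1: reproduce the stated sample size.**
- Normal approximation: n = 2 × (1.645 + 0.842)² × (18.75 / 5.625)² = 2 × 6.18 × 11.11 ≈ 137.4, so 138 per arm.
- Noncentral t: with n = 139 the standard error is 18.75 × √(2/139) ≈ 2.249. The noncentrality is 5.625 / 2.249 ≈ 2.50, on 2 × 139 − 2 = 276 degrees of freedom.
- Power is 0.7998 at 138 per arm and 0.8023 at 139.

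The stated 139 is therefore exact for a t-test on means. The calculation contains nothing about ranks.

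**Step 2: simulate both branches at the margin.** These inputs are assumptions, because the protocol gives no mean, range, shape or switching criterion:
- Control scores are normal, or gamma with mean 25 and SD 18.75. A higher score is taken as worse.
- There are 139 women per arm and 5,000 trials per scenario.
- The switch is taken as a Shapiro-Wilk test at 0.05 in either arm.
- The rank-sum test is given its best case: 5.625 is subtracted from each study-arm score before ranking.

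Every scenario has a true mean difference of exactly 5.625, so a valid test declares non-inferiority in 5% of trials:
- pure shift: every score rises by 5.625;
- proportional increase: every score is multiplied by (25 + 5.625) / 25 = 1.225;
- badly affected minority: 0.15 × 37.5 = 5.625;
- larger, milder minority: 0.30 × 18.75 = 5.625.

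| Scenario at the margin | t-test | Shifted rank-sum | Switch taken | Two-stage rule |
|---|---|---|---|---|
| Normal, pure shift | 0.054 | 0.054 | 9% | 0.054 |
| Gamma, pure shift | 0.051 | 0.051 | 100% | 0.051 |
| Gamma, proportional increase | 0.058 | 0.191 | 100% | 0.191 |
| Gamma, 15% worse by 37.5 | 0.049 | 0.217 | 100% | 0.217 |
| Gamma, 30% worse by 18.75 | 0.052 | 0.075 | 100% | 0.075 |

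The simulation standard error at 0.05 is √(0.05 × 0.95 / 5,000) ≈ 0.003. Repeat runs gave about 0.18 to 0.19 for the proportional increase and 0.21 for the 15% minority.

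**Step 3: why the ranks differ.** Under the proportional increase a woman with control score x worsens by 0.225x. That is below 5.625 whenever x < 5.625 / 0.225 = 25, which holds for most women in a right-skewed distribution with mean 25. After the margin is subtracted, most of the study arm looks better than control, and the large worsening in the upper tail counts only through ranks. In the 15% scenario, 85% of the study arm gains a spurious 5.625-point advantage.

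**The case against.** Four points can fairly be made on the other side.

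*The intended criterion can be identified.* The Sample Size section names a one-sided t-test in means, a margin and an alpha. That stands, and it is why one sentence is enough to reconcile the sections. But the analysis section states a rule that departs from it. This is not detail left to an SAP.

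*The rank-sum test can be used with a margin.* A reader might infer that the 5.625 criterion has no meaning under the rank-sum branch. That goes too far. A shifted test, or a Hodges-Lehmann limit in score points, is available. In simulations with beta scores assumed on a 0 to 100 range (means 20 to 40, SD 18.75), the shifted test kept its error at about 4% to 5%. With identical gamma arms it had more power than the t-test (0.917 against 0.797). The valid objection is narrower: it answers the protocol's question only under a pure location shift.

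*The fallback is not shown to be likely.* A reader might infer that a bounded questionnaire score will almost certainly trigger the switch. The protocol gives an SD and nothing on shape, and it names no normality test. The 100% switching above follows from the assumed gamma shape and the assumed Shapiro-Wilk rule. With normal scores the two-stage rule did no harm (error 0.054, power 0.813).

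*An ordinary rank-sum test that misses a difference at the margin is not evidence against ranks.* In the beta scenarios a two-sided rank-sum test was non-significant in 14% to 33% of trials at the margin, but a two-sided t-test was non-significant in 29% to 31%. That shows the weakness of reading any conventional difference test as non-inferiority, and it applies to both branches.

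**Conclusion.** The point holds in a limited form. The protocol defines its margin and sample size on a mean difference, then allows the observed distribution, by an unstated criterion, to move the primary comparison to a test that does not target that difference. The sample size itself is correct.

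The size of the harm depends on the form of the effect. With the assumed gamma scores, false non-inferiority at the margin is about 0.05 under a pure shift and 0.075 with a larger, milder minority. It is about 0.18 to 0.22 with a proportional increase or a badly affected 15%. The t-based test stays between 0.049 and 0.058 in all five scenarios, so skewness of this degree gives no reason to leave it at 139 per arm. These figures rest on assumed distributions and illustrate what could happen. They do not predict what this trial's scores will do.

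**What to change.** Replace the two-branch rule in the Statistical Analysis section with a single primary analysis, fixed in advance and applied whatever the distribution. It is the difference in mean DCS, abbreviated minus standard, with its t-based one-sided 95% confidence limit (Student or Welch) compared with 5.625. State whether a higher score is worse, because a one-sided limit needs that direction. With the common SD and equal arms that the protocol assumes, Student and Welch will differ little, so either will do if it is named.

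A bootstrap interval for the mean difference, the rank-sum test, or both may stay as sensitivity analyses, labelled as such and with no part in the non-inferiority conclusion.

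The cost is about one sentence. The sample size stays at 139 per arm (power 0.802), and data collection does not change.
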